### Study design

A pragmatic stepped-wedge cluster-randomized approach will be applied, providing Text4Support and Peer Support Service (PSS) to 10,000 participants recruited across 9 acute care sites and day hospitals across Alberta as the clustered unit of randomization (Fig. 1). The design reconciles constraints under which policy makers and service managers operate with the need for rigorous scientific evaluations. In a stepped-wedge study, the design is extended so every cluster provides pre-post observations, and switches from control to intervention exposure but not at the same time-point [42].

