### Sample size considerations

We anticipate a reaching a target sample of 10,000. This figure is about 50% of expected psychiatric discharges, based on the 2018 administrative data (*n* = 20,747) [48]. We decided not to present detailed power analysis for sample size, which is controversial for stepped-wedge design approaches [49]. Further, our study is a pragmatic trial aiming to cause change in real-world conditions, rather than an explanatory trial which aims to study under ideal conditions. Thus, our approach is guided by the Pragmatic-Explanatory Continuum Indicator Summary 2 (PRECIS-2) toolkit with which we aim to align with the higher scores in pragmatism [50].

With our intended 5 randomized clusters and targeted overall project clinical population sample size of 10,000 (including accounting conservatively for 20% patient dropout and 10% dropout for PSWs), we are confident that our sample sizes are more than adequate as we expect at least medium-effect sizes, consistent with our prior results with supportive text messaging programs in Alberta [51].

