### Data analysis

We will conduct preliminary analysis at the end of Q2 (see Fig. 1) and continue to monitor clinical and economic results at each six-month period over years 1-3, culminating in final analysis at the end of Q2 year 3. Primary outcome measurements will be extracted from administrative data, and distribution of primary outcomes data across unexposed observation periods will be compared with the exposed observation periods. Characteristics of individuals/clusters will be summarized by exposure status to allow consideration of selection biases and lack of balance [42].

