Using data from the first preliminary data analysis at the end of Q2 and refining this at each subsequent analysis, we will perform conventional regression methods to predict characteristics and risk factors for patients usually readmitted for inpatient psychiatric treatment within 30 days of discharge. We will further perform machine-learning analysis to predict individuals who may be at risk of readmission within 30 days of discharge at each step. After the first cluster is followed-up, at each step of the stepped-wedge process, we will train a machine-learning model based on existing clusters and test the accuracy of their predictions in the next cluster being followed-up. The potential predictors (features) will include all demographic variables (e.g., age, sex, gender, employment, relationships and housing status, education) and clinical/administrative variables (e.g., diagnosis, substance misuse co-diagnosis, mental and physical comorbidities, presentations to the ED or utilization of crisis services over the period, number of readmissions in the previous year, types of psychotropic medications patient is taking, depot injection or not, Community Treatment Order or not, whether the individual has a General Practitioner or not, and has significant family support or not). The candidate machine learning algorithms will include commonly-used regularized logistic regression based on ElasticNet [55], support vector machines (SVM) and random forest [56, 57]. We will perform feature-, model- and parameter-selection within the training data. The machine learning model could be used for future predictions of readmission but will only be validated in this project and will not be used to intervene the stepped-wedge approach, so that the internal validity and random sampling will be maintained. We hope by the end of the project, we will develop a machine learning model to differentially support individuals at risk of 30-day readmission within 30 days of their discharge with peer support.

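### The readmission model is tested one cluster ahead: a valid but inefficient scheme that tests the near-final model in a single cluster and gives no performance estimate for a model refitted on all clusters

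*Protocol article*

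**What the plan says.** The Data analysis section of the protocol article sets out the split for the machine-learning model of 30-day readmission. It begins "After the first cluster is followed-up, at each step of the stepped-wedge process", and continues: "we will train a machine-learning model based on existing clusters and test the accuracy of their predictions in the next cluster being followed-up". Two safeguards follow. The first is "We will perform feature-, model- and parameter-selection within the training data". The second is that the model "will only be validated in this project and will not be used to intervene the stepped-wedge approach". The section ends with the hope that the project will yield a model for directing peer support to people at risk.

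The Study design section describes a stepped wedge in which "every cluster provides pre-post observations, and switches from control to intervention exposure but not at the same time-point". In line with this, the Data analysis section states for the primary outcome that the "distribution of primary outcomes data across unexposed observation periods will be compared with the exposed observation periods".

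The number of clusters matters for the size of the problem. Sample size considerations says "With our intended 5 randomized clusters and targeted overall project clinical population sample size of 10,000", while Study design names 9 sites and day hospitals as the randomized unit. The numbers expected per cluster and period are in Fig. 1, which is not available here.

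**The concern.** The split is worded as if clusters became available one after another. In the design described, a cluster that has not yet switched already has discharged patients with recorded readmission outcomes. The text does not define an *existing* or a *next* cluster by period or exposure, and it does not say what happens to the control-period patients of clusters still waiting.

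Three consequences follow from the plain reading, in which *existing* means already switched and followed up:

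- Early models are trained on part of the data in hand.
- Each model is tested in one cluster. The successive tests assess models of different training size, and only the last is close to the final model.
- After the last cluster there is no next one, so a model refitted on all clusters, which is the natural one to carry forward, has no performance figure of its own.

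At stake is how well the project can say its risk model performs, given the stated hope of using it to direct peer support. The trial's primary comparison is not at stake.

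**Working it through.** The protocol gives no sample size or precision for the risk model, so there is no figure of its own to reproduce. What follows is illustrative.

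**Inputs**

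- Total of 10,000 participants (Sample size considerations).
- Clusters: 5 (Sample size considerations) or 9 (Study design), assumed equal in size.
- 30-day readmission rate: not given. The Background cites a 90-day rate of up to 14.0% with a median time to readmission of 24 days. Half of 14.0% is 7.0% by day 24, so I take 7% to 14% as the range and 8% as a working value. This is an assumption.
- True AUC of 0.70: assumed.

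**1. Training data under the two schemes (5 clusters of 10,000/5 = 2,000)**

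Next-cluster training sets, counting whole clusters: 2,000, 4,000, 6,000 and 8,000, mean 5,000. Leave-one-cluster-out trains on 10,000 - 2,000 = 8,000 in every fold. The ratio is 5,000/8,000 = 0.625. With 9 clusters the training sets also average 5,000, against 8,889 per fold, a ratio of 0.56.

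**2. Share of data in hand that the early models use**

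This step also assumes that all 5 clusters are observed from the first of 6 equal periods, with one switching per step. One cluster-period then holds 10,000/30 = 333 patients. After step s, 5 x (s+1) cluster-periods have been collected, of which s x (s+1) lie in switched clusters, so the share used is s/5.

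| Step | Collected so far | In switched clusters | Share |
|---|---|---|---|
| 1 | 3,333 | 667 | 20% |
| 2 | 5,000 | 2,000 | 40% |
| 3 | 6,667 | 4,000 | 60% |
| 4 | 8,333 | 6,667 | 80% |

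The percentages depend on the schedule, which is in Fig. 1. The direction does not: every cluster has a pre-switch phase, so some control-period data exist before it switches.

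**3. Precision of the test AUC**

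Hanley-McNeil, with n1 events and n0 non-events:

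SE² = [A(1-A) + (n1-1)(q1-A²) + (n0-1)(q2-A²)] / (n1 n0), where q1 = A/(2-A) and q2 = 2A²/(1+A).

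For A = 0.70: q1 = 0.5385, q2 = 0.5765, q1-A² = 0.0485, q2-A² = 0.0865.

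One cluster of 2,000 at 8% has n1 = 160 and n0 = 1,840. SE² = (0.21 + 7.71 + 159.02)/294,400 = 0.000567, SE = 0.0238, half-width 1.96 x 0.0238 = 0.047.

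All five left-out clusters at 8% have n1 = 800 and n0 = 9,200. SE² = (0.21 + 38.72 + 795.44)/7,360,000 = 0.000113, SE = 0.0106, half-width 0.021.

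| Test set | Rate | Events | 95% half-width |
|---|---|---|---|
| 1 of 5 clusters (2,000) | 7% | 140 | 0.050 |
| 1 of 5 clusters | 8% | 160 | 0.047 |
| 1 of 5 clusters | 14% | 280 | 0.036 |
| 1 of 9 clusters (1,111) | 8% | 89 | 0.063 |
| All clusters, each left out once | 7% | 700 | 0.022 |
| All clusters, each left out once | 8% | 800 | 0.021 |
| All clusters, each left out once | 14% | 1,400 | 0.016 |

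The formula treats patients as independent and ignores differences between clusters, so the pooled figure does not say how the model would do in a new site. For that reason the cluster-specific results are needed beside it.

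**The case against.** The strongest reply is that the planned scheme is a recognised forward validation: train on some clusters, test in a different and later one, and keep all selection and tuning in the training data. It resembles future use, which is predicting later patients at a new site. Leave-one-cluster-out may train on later patients to predict earlier ones. This stands, and it is why the forward test should be kept.

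A second reply is that the planned tests can be pooled. Four next-cluster tests at 8% give 4 x 160 = 640 events and a half-width of about 0.023, almost the 0.021 of the alternative. The arithmetic is right. But the four tests assess models trained on 2,000 to 8,000 patients, so the pooled value describes no single model, and only the last test concerns one near final size.

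A third reply is that a model refitted on all clusters is not itself tested under leave-one-cluster-out either. That is true. But the pooled figure then comes from the same procedure run on 8,000 of the 10,000 patients in every fold, which is a fair basis for the refitted model. The protocol also does not say that a refitted model will be adopted.

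A reader might infer more than the document supports:

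- *That the test is not held out.* Leakage would need the test cluster's own control-period patients in the training set. The text trains on one group of clusters and tests in another, and does not say this.
- *That all clusters contribute from the start.* Study design says only that each gives observations before and after switching. The schedule is in Fig. 1.
- *That early models are badly overfitted.* The candidates include ElasticNet, which regularizes, with selection inside the training data. Few events per predictor do not by themselves establish overfitting for such methods.
- *That data are wasted.* Test data are used, and training grows at each step. At the last step it equals a leave-one-cluster-out fold when whole clusters are counted.

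**Conclusion.** The concern holds as one of efficiency and of what can be reported, not of validity. The one-cluster-at-a-time wording fits poorly with a design in which clusters waiting to switch already supply control-period patients. On the plain reading, early models omit those patients, and the near-final model is judged in one cluster, with an AUC half-width of about 0.05 (7-8% readmission) or 0.04 (14%) for 5 clusters, and about 0.06 for 9 clusters at 8%. Leaving each cluster out in turn gives about 0.02. A model refitted on all clusters has no estimate under the stated scheme.

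These figures rest on equal clusters, an AUC of 0.70, the assumed readmission rates, and a test that uses all of the cluster's patients. If the test used only part of a cluster, the single-cluster interval would be wider. The model is a secondary exercise that does not alter the trial, and the primary comparison is unaffected.

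**What to change.** In the Data analysis section:

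- Define *existing* and *next* cluster by period and exposure, and say how control-period discharges from clusters not yet switched are used.
- At the final analysis, use the control- and intervention-period discharges of all clusters with leave-one-cluster-out (internal-external) validation, repeating feature, model and parameter selection inside each training set.
- Report performance by cluster and pooled. If the model is refitted on all clusters, quote the pooled figure for it.
- Keep the planned step-by-step next-cluster test as the forward-in-time check. State that all of the test cluster's patients, including those from its control period, stay out of training.

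The cost is computing time and a few sentences. No extra data are needed, and nothing in the trial's conduct or primary analysis changes. The one drawback, that some folds predict earlier patients from later ones, is covered by the retained forward test.

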## Discussion

Peer support [13] and text message interventions [14, 23] have advantageous impacts on readmission rates, acute care costs, and no-show rates. We expect our intervention to be equally or more effective than previous Text4Hope and Text4Mood interventions. This innovation mitigates geographical access barriers given that it is a text message-based intervention that can be accessed anywhere mobile network service is available.

The Text4Mood program in Alberta’s North Zone improved the psychological treatment gap [26]. With the Text4Mood program, 82% of respondents to a user survey felt the text messages made them more hopeful about managing issues in their lives. 77% thought the text messages made them feel in charge of managing depression and anxiety. 75% felt connected to a support system. Most respondents (83%) felt Text4Mood improved their overall mental well-being, thus impacting their need for hospital-based care. Similarly, the Text4Hope launched in Alberta in response to the COVID-19 pandemic recorded 32,805 subscriptions from Albertans within the first week [64]. This emergency intervention during the pandemic significantly mitigated the need for readmission, a risk for COVID-19 infection, by reducing mental health distress by over 20% during the pandemic [28]. A combination of this supportive messaging intervention with peer support may have an additive effect in improving outcomes. The use of digital health has become very imperative during the ongoing pandemic. The pragmatic nature of this innovation not only delivers evidence-based supportive text messages which can be deployed on any phone with texting function, irrespective of sophistication, it would also test the effectiveness and implementation of peer support delivered through e-platforms like zoom.

### Anticipated risks and limitations

Generally, this intervention portends little risk to participants, health workers, or the general public. Some participants may view this intervention as a replacement for outpatient or community face to face counseling post-discharge from acute care. However, this risk is neither supported by evidence from the literature or knowledge from implementing our predecessor program, the Text4Mood. Despite this, the PSS component of the Text4Support intervention will further eliminate the likelihood of this effect.

PSW burn-out is also a potential risk. To mitigate this risk, each PSW will be assigned a mental health therapist who will provide support and mentorship. Further, psychiatrists will be available to help where needed.

The ongoing COVID-19 pandemic and associated factors may pose risks to participants, researchers, and project implementation. To mitigate this, we will adhere strictly to the University of Alberta’s revised ethics guidelines for COVID-19 as well as the regularly updated guidelines and policies from the national and provincial authorities. Further, applying a pragmatic study design along with implementation science strategies and tools will help navigate the complex evolving study context caused by the pandemic’s other temporal trends. Operational level changes will be documented carefully, guided by RE-AIM and the Pragmatic-Explanatory Continuum Indicator Summary 2 (PRECIS-2) toolkit [50].

We expect the results for the primary, secondary, and exploratory outcome measures to be available within 3 years of project commencement. It is expected that the results will shed further light on the feasibility of using supportive text message combined with peer support interventions in long-term care for discharged psychiatric inpatients in Alberta. The anticipated outcome of the Text4Support & Peer Support project is illustrated in the logic model attached (Details in Fig. 2).

**Fig. 2 Fig2:**
[figure not shown]
The Logic Model of the anticipated outcome for Text4Support & Peer Support program

## Conclusion

This study will demonstrate an innovative approach to providing community-based support to individuals with mental illnesses. The success of this intervention will not only provide evidence on a new management approach, but also contribute to knowledge on how to implement this innovation across varying contexts.

## Data Availability

Not applicable.

## Abbreviations

AMH: Addiction and mental health
AHS: Alberta Health Services
CORE-10: Clinical Outcomes in Routine Evaluation - 10
CBT: Cognitive behavioral therapy
CFIR: Consolidated Framework for Implementation Research
ED: Emergency department
HiMARC: Heroes in Mind, Advocacy and Research Consortium
PHQ-9: Patient Health Questionnaire
PSS: Peer Support Service
PSWs: Peer Support Workers
PRECIS-2: Pragmatic-Explanatory Continuum Indicator Summary 2
QCA: Qualitative content analysis
QD: Qualitative descriptive
QALY: Quality Adjusted Life Year
RE-AIM: Reach-Effectiveness-Adoption-Implementation- Maintenance
RAS: Recovery Assessment Scale
SVM: Support Vector Machines
